## Abstract

Background. Despite ongoing treatment advancements in chronic heart failure (HF), mortality and readmission rates remain high for patients hospitalized for decompensated acute HF. These patients represent a distinct HF group, which requires emergent echocardiographic evaluation in an attempt to provide optimal and individualized acute care. The role of serial advanced echocardiographic assessment in acute HF for risk stratification and treatment guidance has not been thoroughly explored. Methods. The “Beyond Myo-HF Study” is a prospective, non-interventional cohort trial designed to enroll acutely admitted patients with symptoms and/or signs of HF. The aim of this study is to investigate whether intrahospital changes of conventional and novel echocardiographic indices of myocardial function and congestion-related markers can predict early mortality, late mortality, and HF rehospitalization. As per the protocol, all patients undergo a pair of state-of-the-art echocardiographic assessments, with a rigorous protocol including speckle tracking analysis of all cardiac chambers and myocardial work analysis for the left and right ventricle, upon admission and pre-discharge. Their laboratory profile is captured at those two time-points, and their therapeutic management is recorded. Patients will be followed-up for a median period of 12 months after enrollment. Conclusions. The “Beyond Myo-HF” study is an ongoing, prospective trial aspiring to provide deep insight into the pathophysiology of acute HF, to enlighten the reverse cardiac functional and anatomical remodeling during hospitalization, and to recognize echocardiographic patterns capable of predicting adverse outcomes during and post decompensation of acute HF.

## 1. Introduction

Hospitalized patients with acute heart failure (HF) represent an understudied, distinct group of patients which has mainly been characterized through registries [1]. These patients largely differ from stable outpatients with chronic HF in terms of clinical course, and continue to suffer very poor prognosis; they have an estimated mortality and readmission rate of 15% and 30%, respectively, between the first and second month post discharge [2]. In this regard, it is of paramount importance to identify vulnerable subjects in order to intensify their follow-up and outpatient care. Suboptimal echocardiographic improvement in response to acute HF treatment may represent a red flag but current literature is scarce.

In acute decompensated HF, intensive therapy aims to lessen intracardiac pressure and central venous congestion [3], which is expressed as an improvement of the circulatory volume-dependent echocardiographic parameters, mainly evidenced through reverse remodeling of the thin-walled right ventricle (RV). It has been suggested that improvement of RV function surrogates such as tricuspid annular plane systolic excursion (TAPSE) and right ventricular–pulmonary artery (RV–PA) coupling is of prognostic relevance [4]. However, TAPSE has obvious limitations as it poorly reflects overall contractility of the RV [5], and it has been surpassed by speckle tracking echocardiography with longitudinal strain, which is sensitive in detecting dynamic improvement in RV mechanics [6].

Longitudinal strain does not integrate ventricular dyssynchrony into its quantitative output and does not account for the afterload, which is subject to considerable alterations with the intensive acute HF medical therapy particularly for the RV. Myocardial work is a non-invasively derived index of myocardial function that accounts both for ventricular dyssynchrony and afterload [7]. Although originally dedicated for the left ventricle, this method has recently been evaluated for the RV and has shown significant correlation with invasively measured RV stoke volume [8]. Nonetheless, its prognostic implications in the acute HF setting have not been comprehensively investigated so far.

Accordingly, using—among others—novel echocardiographic imaging biomarkers, this observational study aims to investigate (i) the intrahospital echocardiographic variations of diverse acute HF phenotypes as a response to acute treatment, (ii) the improvement or deterioration of all chambers’ systolic function parameters and echocardiographic markers of congestion during the acute HF episode, (iii) the association of admission or discharge echocardiographic parameters with early mortality, late mortality, and HF rehospitalization, and (iv) whether suboptimal echocardiographic improvement at discharge in response to acute HF treatment is associated with poor prognosis.

## 2. Methods and Materials

### Study Design and Population

The “Beyond Myo-HF Study” (ClinicalTrials.gov Identifier: NCT05573997) is an investigator-initiated, prospective, non-interventional cohort trial involving patients with acute HF. A total of 300 consecutive patients acutely admitted to the Department of Cardiology of AHEPA University General Hospital, Thessaloniki, Greece with symptoms and/or signs of HF satisfying the inclusion criteria are enrolled in the present study. Eligibility criteria are described in Table 1.

Demographic characteristics and baseline medical history including a history of previous hospitalization for acute HF, primary etiology, and clinical presentation of hospitalization are recorded for all participants. Pharmacological and non-pharmacological therapeutic maneuvers during the acute phase of hospitalization, as well as medical therapy upon admission and discharge, are collected. A comprehensive transthoracic echocardiographic assessment (TTE) is performed at two different time-points during hospitalization. The first TTE is performed within 24 h from admission, and the second with 24 h pre-discharge, to capture the trajectory and net variations of all echocardiographic indices of interest. A cardiac computed tomography or cardiac magnetic resonance study will be routinely performed as required to investigate the primary HF cause for undiagnosed patients. In addition, patients’ laboratory results including complete blood count, biochemical control, inflammatory markers, coagulation mechanism control, hormonal control, N-terminal pro-B-type natriuretic peptide, and high sensitivity troponin T levels are collected upon admission and prior to discharge (Figure 1).

Before each TTE study, heart rate and brachial blood pressure using a conventional sphygmomanometer are recorded. Additionally, height and weight of each participant are recorded and utilized to determine body mass index and body surface area in accordance with the Dubois formula [9]. Informed written consent is obtained from all participants prior to study enrollment. All patients undergo standard of care acute HF management, as dictated by their clinical presentation, the practice of the hospital, and most updated guidelines [10]. The investigation conforms with the principles outlined in the Declaration of Helsinki (2013 Amendment), and the study protocol was approved by the Ethics Committee of the School of Medicine of Aristotle University of Thessaloniki (Approval number: 19/2022, Date of approval: 10 November 2022).

In accordance with the guideline-recommended HF definitions [10], HF patients are classified on the basis of their left ventricular ejection fraction (LVEF), as this is calculated from the admission TTE study. Those are patients with (i) heart failure with reduced ejection fraction (LVEF ≤ 40%), (ii) heart failure with mildly reduced ejection fraction (LVEF = 41–49%), and (iii) heart failure with preserved ejection fraction (LVEF ≥ 50%). In addition, patient are classified as new-onset or chronic HF, on the basis of a previously documented HF hospitalization. The trend of their echocardiographic profile during hospitalization is recorded to identify predictors of early and late mortality, and HF rehospitalization at follow-up. Follow-up data are collected regularly by independent physicians via in-person or telephonic interviews. All deaths are ascertained by searching in the Greek web-based national health insurance system. Other clinical outcomes, apart from death, are identified either through hospital reports or by telephone contact.

## 3. Materials and Equipment

### 3.1. Echocardiographic Analysis

All TTE studies are performed by certified sonographers/cardiologists using high-end scanners (e.g., Vivid E95, GE Healthcare, Chicago, IL, USA). Electrocardiogram-triggered echocardiographic data are stored offline in a cine-loop format for analysis using proprietary software. All analysis is separately performed by an expert cardiologist, blinded to the clinical data of all participants.

### 3.2. Chamber Quantification Analysis

The size of all cardiac chambers is assessed in accordance with most current recommendations [11]. Two-dimensional and Doppler measurements are performed as recommended [11,12]. Simpson’s biplane method is utilized to calculate left ventricular ejection fraction (LVEF) and abnormal values of conventional left ventricular (LV) diastolic parameters are determined on the basis of recently established criteria [12]. All RV systolic function parameters including TAPSE, fractional area change, and systolic movement of the RV lateral wall (S’) are evaluated as per current guidelines [13]. RV fractional area change is calculated by the formula: Fractional Area Change = ([RV end-diastolic area − RV end-systolic area]/RV end-diastolic area) × 100%. TAPSE is measured by M-mode and S’ by pulse-wave tissue Doppler imaging (TDI) recordings of the lateral tricuspid annulus in an RV-focused view [13]. Estimated right atrial pressure is determined on the basis of the evaluation of inferior vena cava and its collapsibility [13]. Pulmonary artery systolic pressure (PASP) is derived from the tricuspid jet peak velocity and the estimated right atrial pressure using the modified Bernoulli equation [13]. An integrated approach is used to quantify the severity of valvular heart disease in line with the recommendations from the respective guidelines [14,15]. A scale ranging from 1 to 4 to define mitral regurgitation and tricuspid regurgitation severity is employed as suggested by recent published literature [15,16]: grade 1 indicates “mild”, 2 “moderate”, 3 “moderate-to-severe”, and 4 refers to “severe” mitral regurgitation or tricuspid regurgitation.

### 3.3. Strain Analysis

Two-dimensional speckle tracking echocardiography is utilized to calculate strain measurements for all four cardiac chambers. Gain settings and imaging width are adjusted to optimize the grey scale at frame rates of 50–80 Hz. On average, three different measurements are performed, using the onset of QRS as the referent point. LV, RV, and left atrial strain measurements are performed using separate proprietary software originally developed for speckle tracking analysis of each chamber. For the calculation of right atrial strain, software originally developed for the assessment of left atrial strain is utilized. For the LV, images are acquired from the apical four-chamber, apical two-chamber, and apical long-axis view. For the left atrium, images from the apical four-chamber and apical two-chamber view are employed. For the RV and right atrium, images from apical RV-focused view and apical four-chamber view, respectively, are used. Global longitudinal strain (GLS) is derived from calculation of the average of the peak systolic longitudinal strain of all segments for each chamber.

### 3.4. Left Ventricular Myocardial Work Analysis

Calculation of LV myocardial work (LVMW) is performed with the use of a commercially available vendor-specific software package. To estimate myocardial work indices, LV GLS and peak systolic LV pressure measurements are integrated with the aforementioned module, as previously described [7]. The patient’s brachial blood pressure recording is entered into the module as an estimate of peak systolic LV pressure. The latter is assumed to be equivalent to the arterial pressure, as expressed by the brachial blood pressure. Apical long-axis view is utilized to determine opening and closing timings of the aortic and mitral valves as a means to define the different phases of the cardiac cycle. Noninvasive LV pressure curves are formulated according to the duration of ejection and isovolumic phases, as determined by left-sided valve timing events. LV strain and pressure data are synchronized through alignment of the cardiac cycle phases and systolic blood pressure. Four different indices of myocardial work are calculated including (i) LV global work index (LVGWI, mmHg%), representing the total work within the LV pressure–strain loops, (ii) LV global constructive work (LVGCW, mmHg%), defined as the work performed during myocardial shortening in systole and the work during myocardial lengthening in isovolumic relaxation, (iii) LV global wasted work (LVGWW, mmHg%), representing the work contributing to the lengthening of the cardiac myocytes during systole and the shortening during isovolumic relaxation, and (iv) LV global work efficiency (LVGWE, %), defining the percentage of effectively spent work by the LV myocytes and obtained by the following formula: (LVGCW/[LVGCW + LVGWW]) × 100%.

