## Figures and Tables

**Figure 1 diagnostics-13-01191-f001:**
[figure not shown]
Study design diagram. Serial echocardiographic and laboratory assessment will be performed in 300 consecutive patients admitted with acute heart failure, in order to identify predictors of early mortality, late mortality, and heart failure rehospitalization. Abbreviations: ACS, acute coronary syndrome; HFpEF, heart failure with preserved ejection fraction; HFrEF, heart failure with reduced ejection fraction.

**Table 1 diagnostics-13-01191-t001:** Inclusion and exclusion criteria of the “Beyond Myo-HF study”.

Inclusion Criteria	Exclusion Criteria
Symptoms and/or signs of heart failure Abnormal plasma concentration of N-terminal pro-B-type natriuretic peptide, measured within 24 h of admission Objective echocardiographic evidence of cardiac structural and/or functional abnormalities consistent with the presence of LV systolic dysfunction/diastolic dysfunction/raised LV filling pressures upon admission assessment Adult patients	Symptoms and/or signs of HF secondary to congenital heart disease, infective endocarditis, pericardial disease, and history of recent cardiac surgery (<1 month); pulmonary circulation pathologies such as I, IV, V pulmonary hypertension Patients receiving maintenance hemodialysis or peritoneal dialysis Severe liver insufficiency Patients with active malignancy and/or life expectancy <1 year because of comorbidities Heart transplantation Poor echocardigraphic acoustic windows precluding reliable assessment and/or analysis Patients not providing informed written consent to participate in the study

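### LV myocardial work equates peak LV pressure with cuff pressure in every patient, yet acquired aortic stenosis and LV outflow obstruction are not excluded

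*Protocol article*

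**What the plan says.** Section 3.4 (Left Ventricular Myocardial Work Analysis) of the protocol article fixes the pressure input: "The patient’s brachial blood pressure recording is entered into the module as an estimate of peak systolic LV pressure". It then gives the premise: "The latter is assumed to be equivalent to the arterial pressure, as expressed by the brachial blood pressure". There is no gradient term, and no group of patients is exempt. Section 2 (Study Design and Population) says how the pressure is obtained: "Before each TTE study, heart rate and brachial blood pressure using a conventional sphygmomanometer are recorded".

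Section 2 enrols 300 consecutive patients and refers to Table 1 for eligibility. The cardiac causes excluded there begin with "Symptoms and/or signs of HF secondary to congenital heart disease, infective endocarditis, pericardial disease, and history of recent cardiac surgery", followed by certain groups of pulmonary hypertension. Heart transplantation is a separate exclusion. The only imaging exclusion is "Poor echocardigraphic acoustic windows precluding reliable assessment and/or analysis". Acquired aortic stenosis and LV outflow obstruction are not listed, and the congenital exclusion reaches congenital forms only.

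Section 3.2 shows that valve disease is expected in the cohort: "An integrated approach is used to quantify the severity of valvular heart disease". That grading is not linked to the work calculation. Section 5 (Limitations) does not mention the pressure assumption.

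**The concern.** Cuff pressure can stand in for peak LV pressure only when nothing obstructs flow between the ventricle and the arm. With a fixed or dynamic obstruction, the ventricle generates the arterial pressure plus the gradient, so the software receives too low a pressure. The plan admits such patients and applies the same input rule to them.

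This touches the reason for using the index. Section 4 argues that longitudinal strain needs adjustment for afterload in acute HF and that myocardial work supplies it, with blood pressure as the afterload estimate. In an obstructed ventricle the cuff reading omits the obstructive part of the afterload, so the adjustment is incomplete where it is most needed.

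The values are then used in two ways under Section 3.6. Admission and discharge are compared by paired t-test or Wilcoxon signed rank test, and novel imaging markers are tested for added prognostic value by likelihood ratio. An error in the level or the change of LV work enters both.

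**Working it through.** The article gives no gradient, no prevalence of obstruction and no figure for this error, so there is nothing of its own to reproduce. What follows is an illustration under stated assumptions.

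**Inputs**

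- From the article: peak LV pressure is set to cuff systolic pressure P (Section 3.4); N = 300 (Section 2); LVGWE = LVGCW/(LVGCW + LVGWW) × 100% (Section 3.4).
- Assumed: P of 100 to 120 mmHg for the level; a systolic LV-aortic gradient G of 20 to 50 mmHg in affected patients; work approximated as peak LV pressure × s, where s is the absolute value of GLS.

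**Step 1: error in the level.** True peak LV pressure is P + G and the entered pressure is P. The understatement is 1 − P/(P + G) = G/(P + G).

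| P (mmHg) | G (mmHg) | Understatement |
|---|---|---|
| 120 | 20 | 20/140 = 14.3% |
| 120 | 40 | 40/160 = 25.0% |
| 120 | 50 | 50/170 = 29.4% |
| 100 | 20 | 20/120 = 16.7% |
| 100 | 50 | 50/150 = 33.3% |

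With G = 0 there is no error. Under the approximation, LVGWI, LVGCW and LVGWW are understated in the same proportion.

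**Step 2: error in the change.** With 1 for admission and 2 for discharge, the cuff-based change is P2·s2 − P1·s1. The change with the gradient included is (P2 + G2)·s2 − (P1 + G1)·s1. The part missed is G2·s2 − G1·s1. Take P falling from 140 to 120 mmHg and s rising from 10 to 12% (assumed). The cuff-based change is 120 × 12 − 140 × 10 = +40 mmHg%, whatever the gradient.

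| G1 to G2 (mmHg) | Change with gradient included (mmHg%) |
|---|---|
| 0 to 0 | 1,440 − 1,400 = +40 |
| 40 to 40 | 1,920 − 1,800 = +120 |
| 50 to 40 | 1,920 − 1,900 = +20 |
| 40 to 20 | 1,680 − 1,800 = −120 |

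A constant gradient does not cancel, because it is multiplied by a strain that changes. The error vanishes only if G2·s2 equals G1·s1. The last row shows that even the sign can be wrong.

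**Step 3: efficiency.** If the pressure is off by a common factor k, LVGWE = k·LVGCW/(k·LVGCW + k·LVGWW), and k cancels. With illustrative values of 1,500 and 150 mmHg%, LVGWE is 1,500/1,650 = 90.9% for k = 1 and also for k = 1.33. The cancellation is exact only for uniform scaling, hence largely rather than fully spared.

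**Step 4: dilution over the cohort.** The share affected is unknown. If it were 5 to 15% (assumed), 15 to 45 of 300 patients would be involved. With similar true work in affected and unaffected patients, the average understatement would be between 0.05 × 14.3% = 0.7% and 0.15 × 33.3% = 5.0%.

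**The case against.** The strongest reply is that this is a condensed article. It calls the cuff reading an estimate, says openly that equality is assumed, and follows a cited published method. A rule limiting LV work to certain patients is an analysis-set matter that could stand in the full protocol or SAP, and it need not appear in Table 1, which governs enrolment. This stands in part: such a rule may exist elsewhere. But the point does not rest on silence alone. The article states an input rule without limits and an eligibility list that admits patients in whom the rule fails. Followed as written, it gives wrong values in them.

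A second reply is that the size is assumed throughout and that the per-patient error dilutes to a few per cent across the cohort. This also stands. LV work is moreover one family among many indices, and the others do not use cuff pressure as LV pressure.

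A third is that the data can be rescued later: valve severity is quantified, primary etiology is recorded and images are stored offline. That is true, and it makes the fix cheap. It does not remove the need to set the rule before the associations are seen.

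A reader might also infer that obstructed patients are at higher risk, so that the error is tied to outcome and creates or inflates a work-outcome association. The documents do not support this. They give no risk for these patients relative to other acute HF patients, whose prognosis Section 1 already describes as very poor, and no such bias has been estimated.

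**Conclusion.** The point holds for three of the four LV work indices, in a subgroup whose size is unknown. Wherever there is a systolic LV-aortic gradient, the stated input rule understates LVGWI, LVGCW and LVGWW. For an affected patient with SBP 120 mmHg, the error is 14 to 29% if the gradient is 20 to 50 mmHg. The change between the two studies is distorted when strain or gradient differs between them, unless the two differences happen to offset. LVGWE is largely spared.

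The direction of the error in level follows from the physics and needs no assumed figure. Its size rests on the assumed gradients and on treating work as proportional to peak pressure. It would be wrong to read this as saying that LV work is invalid for the cohort as a whole, or that the prognostic results are biased in a known direction.

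**What to change.** Add an analysis rule to Section 3.4 or 3.6. Enrolment and care do not change.

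1. **Main analysis.** Leave patients with more than mild aortic stenosis or a relevant LV outflow gradient on either TTE out of the LVGWI, LVGCW and LVGWW analyses only. Keep them in all others. Define a relevant gradient in advance and report the number left out.
2. **Sensitivity analysis.** Include these patients. For valvular aortic stenosis, add the Doppler transvalvular gradient from the same TTE to the cuff pressure, and name in advance which Doppler gradient is used, since the sum is itself an approximation. Do not apply this correction to dynamic subvalvular obstruction, which a transvalvular gradient does not represent.
3. **Limitations.** State in Section 5 that LV work assumes no LV-aortic gradient.

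If the full protocol or SAP already contains such a rule, a sentence in the article pointing to it is enough.

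The cost is a modest loss of patients in the analyses of three indices and re-entry of pressure for a minority of scans. Valve severity, etiology and Doppler measurements are already collected under Sections 2 and 3.2. The team should check that any outflow gradient is recorded at both studies.

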### 3.5. Right Ventricular Myocardial Work Analysis

RV myocardial work (RVMW) indices analysis is performed by adapting proprietary software originally developed for the assessment of LVMW, as previously described [8]. Similar to the non-invasive method for evaluation of LVMW, initially developed by Russel et al. [7], the RV myocardial force–segment length loops are estimated with pressure–strain loops. PASP and pulmonary artery diastolic pressure (PADP) are entered in the software instead of systolic blood pressure and diastolic blood pressure. Pulmonary artery mean pressure (PAMP) is derived from the following formula: mean RV-right atrial gradient + mean right atrial pressure [17]. Tracing of the tricuspid regurgitation velocity–time integral is used for mean RV-right atrial pressure calculation. PADP is estimated as PADP = 1.5 × [PAMP − (PASP/3)] [13,17].

An approximation of the RV myocardial force is derived from pulmonary pressure estimates, and changes in segment length are obtained from speckle tracking echocardiography-derived strain analysis. RV global longitudinal strain (GLS), including both RV free wall and interventricular septum, are obtained from RV-focused apical four-chamber view. Pulse-wave interrogation in the basal parasternal short-axis view is applied to define timings of pulmonary valve opening and closure, whereas timings of tricuspid valve opening and closure are obtained by direct visualization of leaflets on RV-focused apical four-chamber view. RV GLS, and PASP, and PADP measurements are synchronized by right heart valve events to generate non-invasively derived pressure–strain loops for the RV. Four separate parameters of RV function are derived from the pressure–strain loops analysis. They include (i) RV global work index (RVGWI, mmHg%), calculated from the area within the global RV pressure–strain loop, (ii) RV global constructive work (RVGCW, mmHg%), an estimate of the work contributing to myocardial shortening during systole and lengthening during isovolumic relaxation, (iii) RV global wasted work (RVGWW, mmHg%), representing the work contributing to the lengthening of the cardiac myocytes during systole and the shortening during isovolumic relaxation, and (iv) RV global work efficiency (RVGWE, %), defined as the percentage of effectively spent work by the RV myocytes and obtained by the following formula: (RVGCW/[RVGCW + RVGWW]) × 100% [8].

